## Abstract

**Background:**

Breast cancer patients face significant psychological challenges, including difficulties in accepting the diagnosis, treatment, and long-term impact of the disease. Acceptance and Commitment Therapy (ACT) has shown promise in enhancing acceptance and psychological flexibility in various populations. This study aims to investigate the effectiveness of ACT in promoting disease acceptance among breast cancer patients through a randomized controlled trial.

**Methods:**

This study will recruit 90 breast cancer patients and randomly allocate them to an ACT intervention or control group. The ACT intervention, focusing on acceptance, mindfulness, value clarification, and committed action, will be delivered over 4 weeks. Meanwhile, the control group will receive standard care with non-therapeutic intervention. The study’s primary outcome is disease acceptance, while secondary outcomes include depression, anxiety, social support, quality of life (QoL), and psychological inflexibility. Data will be collected at three points: baseline, post-intervention, and three-month follow-up. Statistical analysis will compare outcomes between groups to evaluate the effectiveness and mechanism of this intervention using covariance and mediation analysis.

**Discussion:**

This study evaluates the effectiveness of ACT in promoting disease acceptance among breast cancer patients. It hypothesizes that the ACT group will show higher disease acceptance and improvements in social support, QoL, and psychological flexibility compared to the control group. The findings will contribute to research on psychological interventions and demonstrate ACT’s effectiveness in enhancing disease acceptance.

**Trial registration:**

The research project is registered in the ClinicalTrials (NCT05327153).

## Introduction

Breast cancer is a widespread and impactful health issue that significantly impacts the lives of numerous women across the globe. By 2020, there will be 2,179,457 new breast cancer cases in women globally, making up 24% of all new cancer cases in women, predicts the World Health Organization (WHO). Contrarily, breast cancer has a good prognosis and a protracted survival period. In some developed regions, the five-year standardized relative survival rate for breast cancer exceeds 80% [1]. Breast cancer has a high incidence, but its survival rate is generally more significant than most other cancers, which means that long-term survival rates are improving. However, most patients’ QoL is poor [2]. In addition to the physical hurdles, breast cancer frequently leads to significant psychological distress and emotional upheaval among patients. Malignant tumors are often linked to death in the minds of patients. Patients are under great psychological stress while dealing with the physical discomfort caused by the condition. Anxiety and despair are common negative emotions [3]. The psychological state of cancer patients is influenced by the diagnosis, complications, and treatment side effects [4]. Breast cancer patients had a greater rate of mental disorders after diagnosis than the general population, with 42% meeting rigorous diagnostic criteria for mental disorders within four weeks of diagnosis, the highest rate of all cancers [5]. Additionally, breast cancer patients are more likely to experience subclinical psychological problems and symptomatic psychological discomfort, with frequencies ranging from 30% to 75% [6]. The impact of these psychological problems on patients’ QoL is profound. Psychological distress can exacerbate physical symptoms, interfere with treatment adherence, and negatively influence overall well-being and recovery [7]. Anxiety and depression can lead to decreased motivation, social withdrawal, and impaired cognitive functioning in daily activities [8]. Furthermore, negative emotions can strain personal relationships and support systems, making it more challenging for patients to cope with their diagnosis and treatment [9]. Therefore, finding ways to enhance the psychological rehabilitation of breast cancer patients is crucial in oncology. Effective psychological support and interventions are essential to improve the overall QoL and aid in the holistic recovery of breast cancer patients.

Disease acceptance, which refers to the capacity to recognise and adjust to breast cancer’s diagnosis, treatment, and long-term consequences, significantly influences patients’ overall well-being and adaptation [10]. However, many individuals diagnosed with breast cancer struggle to accept their condition. These difficulties include dealing with the fear of recurrence, coping with body image changes due to surgery and treatments, managing the side effects of chemotherapy and radiation, and financial stress [11]. These challenges contribute to increased emotional distress, reduced QoL, and difficulties in effectively managing their treatment and survivorship. According to a recent study, 20% of breast cancer patients following mastectomy still struggle to accept their diagnosis [12]. Empirical research on acceptance intervention found that those who underwent it and were exposed to unpleasant interoceptive stimuli exhibited less behavioral avoidance, intense dread, cognitive panic symptoms, and catastrophic thoughts [13]. Good acceptance can effectively reduce individual anxiety levels [14]. Furthermore, due to the shift in the modern medical model, breast cancer treatment now focuses on extending patients’ survival times, lowering mortality, and improving their QoL [15]. Meanwhile, social support can encourage breast cancer patients to utilize positive coping strategies, increase their cognitive understanding of the disease, boost their self-esteem, and improve their QoL [16]. The most important aspect of the adaptation process is accepting the disease. Better disease acceptance can lead to less stress and higher self-esteem, making adjusting to new health statuses easier. As a result, this study aims to see if boosting illness acceptance improves breast cancer patients’ psychological well-being.

In response to the psychological effects of breast cancer, researchers and practitioners have investigated a range of therapeutic approaches. Studies have shown that psychotherapy may reduce cancer patients’ psychological suffering, ease their anxiety and sadness, and enhance their QoL [17]. The development of psycho-oncology has led to increased use of psychological interventions in breast cancer patients, recognizing the significant impact of mental health on overall well-being and treatment outcomes [18–20]. Several psychological interventions have been employed to support breast cancer patients, including cognitive-behavioral therapy (CBT), mindfulness-based stress reduction (MBSR), supportive-expressive therapy, and psychodynamic therapy. These interventions aim to address various aspects of psychological distress, such as anxiety, depression, fear of recurrence, and body image concerns, thereby improving patients’ QoL and ability to cope with their diagnosis and treatment [21]. Among these approaches, ACT stands out.

ACT is a contemporary form of cognitive-behavioral therapy that emphasizes the importance of psychological flexibility. This flexibility is the ability to fully engage with the present moment and persist or change behavior in a way that aligns with personal values, even in the presence of challenging thoughts and feelings. Grounded in Relational Frame Theory (RFT) [22], ACT incorporates mindfulness and acceptance strategies alongside commitment and behavior change techniques to help individuals live a more meaningful and value-driven life. The six core processes of ACT are acceptance, cognitive defusion, being present, self as context, values, and committed action. Together, these processes aim to reduce the influence of unhelpful thoughts and feelings, enabling individuals to pursue their goals and values more effectively [23].

ACT has demonstrated feasibility and promise across various contexts for breast cancer patients. It has shown potential in improving fatigue and sleep-related outcomes in breast cancer patients [24]. ACT is also effective in managing fear of cancer recurrence and associated significant improvements in avoidant coping, anxiety, depression, and QoL [25]. Additionally, ACT has proven to be an effective intervention for reducing depression and enhancing psychological flexibility among breast cancer patients [26]. Even a single-session ACT intervention has yielded small but positive improvements in postsurgical pain and anxiety, reinforcing its utility in this population [27]. ACT may enhance disease acceptance by encouraging patients to accept their negative emotions, thoughts, and physical sensations related to their cancer diagnosis and treatment, thereby reducing the impact of these negative thoughts and feelings on their daily lives. By fostering acceptance and mindfulness, ACT helps patients reframe their perception of the stressors associated with breast cancer, viewing them as manageable aspects of their lives rather than overwhelming threats. Furthermore, ACT emphasizes identifying personal values and committing to actions consistent with these values, even in the face of discomfort. This value-driven focus can reduce the perceived burden of the disease and improve patients’ overall QoL, making it easier for them to accept their condition and its long-term consequences. By promoting psychological inflexibility, ACT enables patients to adapt more effectively to their illness, facilitating better disease acceptance and QoL.

In one study, ACT is used to help breast cancer patients feel better about their lives and mental health. Jing Han et al. (2009) showed that ACT intervention effectively enhanced psychological inflexibility, disease cognition (including acceptance), and QoL [28]. However, no randomized controlled trial was carried out to verify the outcomes of this early investigation. This study aims to close that knowledge gap by conducting an RCT to evaluate the effectiveness of ACT in improving psychological inflexibility, disease acceptance, and QoL among breast cancer patients. Specifically, it seeks to provide fresh perspectives on how enhancing acceptance of the diagnosis through ACT can directly impact the QoL in breast cancer patients. Although there is strong evidence linking breast cancer patients’ psychological inflexibility, depression, anxiety, and QoL, the process is still not fully understood [29]. This study aims to investigate how ACT enhances the QoL in breast cancer patients by examining the potential mediating factors of psychological inflexibility and disease acceptance. The findings of the mediation analysis will help establish evidence for the mechanism of action for ACT’s efficacy.

Moreover, social support can encourage patients to use positive coping strategies and reduce the use of negative ones. A study involving 90 breast cancer patients administered supportive intervention revealed significant improvements in body image, physical and mental health, and various functions [30]. Therefore, in our study, social support will be a moderator variable to illustrate the change in illness cognition, psychological inflexibility, depression, anxiety, and QoL according to ACT intervention, thus further elucidating the mechanism of change. Overall, the results of the mediation and moderation analysis will contribute to the advancement of knowledge, the development of novel theories, and the enhancement of ACT treatment efficacy to patient requirements.

Overall, our study aims to assess the ACT intervention thoroughly, bridge the existing gap in the literature, and offer evidence-based suggestions for healthcare professionals and clinicians who support individuals with breast cancer. Ultimately, our findings have the potential to guide the development of tailored interventions that enhance disease acceptance, improve psychological well-being, and contribute to the long-term adjustment and overall QoL for breast cancer patients.

## Objective

### Primary objective

To compare the efficacy of ACT in enhancing disease acceptance compared with the waitlist control group across three-time points (T0 = baseline assessment, T1 = 4 weeks, immediately after completion of the intervention, T2 = 6 months after commencement of the intervention, and T3 = 12 months after commencement of the intervention).

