### Participants

Patients receiving treatment in oncology clinics at Universiti Sains Malaysia and Hospital Seberang Jaya will be recruited for the study. The criteria for study participation include: (1) diagnosed with breast cancer, (2) aged 18 years or older, (3) currently receiving treatment, (4) able to understand and communicate in the study language, and (5) willing to participate in the intervention and follow-up assessments. Patients are deemed ineligible for the study if they: (1) have severe cognitive impairment or significant psychiatric comorbidities (e.g., psychosis, substance abuse) that could hinder their participation in the study, (2) are diagnosed with malignant tumors, and (3) currently receiving any other form of psychological therapy intervention.

Sample size calculations will be based on power analysis using established effect sizes from previous studies on ACT interventions and disease acceptance among similar populations. We conducted an a priori power analysis using GPower 3.1.9.7 to calculate the estimated sample size needed for mixed ANOVA with control of three covariates: the type I error was 0.05, with a power of 0.95, three covariates, with two intervention groups and an effect size of 0.46 by referring to an RCT on the efficacy of ACT on illness cognition among breast cancer patients [28], Hence, the estimated sample size needed is 80 (with the inclusion of a 20% dropout rate). Hence, 40 subjects are required per group.

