### Procedure

This research used a consecutive sampling technique for subject recruitment before randomly assigning them to the intervention and control groups. Potential participants will first be screened to determine their eligibility for study participation. Invitations to take part in this trial will follow. The investigator will ensure that participants receive a thorough explanation of the study goals and methods before agreeing to join the study. Participants will sign the Subject Information and Consent Form and Participant’s Material Publication Consent Form before enrolling in the research to indicate their agreement. We will ensure the participants’ anonymity and inform them about their right to withdraw from the study at any point, guaranteeing their confidentiality and autonomy. To ensure participants receive similar intervention, the trial adapts a brief ACT module by Shari et al. [31]. The therapist will administer the intervention when patients are in the hospital for treatment. The assessment batteries will be issued at three specific time points: before the intervention, immediately after the intervention, and three months following the intervention.

Participants in the control group will receive the non-therapeutic approaches, such as reassurance, to allow patients to ventilate their problems and to conduct relaxation techniques such as deep breathing. The intervention and the control groups will receive a 4-session program to ensure ethical considerations and participant access to the intervention. The enrolment, interventions, and assessments of the study are summarized in Fig 1. Fig 2 shows the flow of the research procedures and outcome measures.

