## Interventions

### ACT intervention

ACT is one of the most representative experiential behavior therapies in the third wave of cognitive and behavior therapy, called “contextual cognitive-behavioral therapy.” ACT aims to increase psychological flexibility so that people may dedicate themselves to a worthwhile and meaningful life via flexible therapeutic methods, as well as mindfulness, acceptance, defusion, self as context, value, and committed action. The interventions include evaluating cognitive fusion and values, accepting negative emotions and experiences, dissociating from personal experience, contact with the present and meditation training, determining importance, making behavior plans, etc. The ACT intervention is scheduled for 1 session per week for 4 weeks. Each session lasts for 1 hour. The activities in each session are summarized in Table 1. A detailed description of the activities in each session is presented in the S1 Appendix.

**Table 1 pone.0312669.t001:** Summary of content of ACT treatment sessions.

Session	Element in hexaflex	Content
Introductory	Therapeutic relationship, introduction to ACT	Establish a therapeutic relationship, conduct an intake interview (patient’s background, illness, coping mechanisms), develop a case formulation, and introduce ACT principles.
Let it go	Acceptance and defusion	Teach acceptance of unpleasant thoughts and emotions, use metaphors (e.g., tug-of-war with a monster) to practice cognitive defusion, reduce avoidance, and encourage observation of thoughts. Two home exercises on acceptance and defusion provided.
Show up	Contact with present moment, self-as-context	Mindfulness exercises to develop present-moment awareness and non-judgmental observation of thoughts, guide patients to view thoughts flexibly, and practice mindfulness exercises (e.g., mindful breathing).
Get moving	Values and committed action	Help patients identify values, set value-driven goals, guide action steps toward meaningful activities, and provide four home exercises (e.g., values assessment, mindfulness exercise).

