## Statistical analysis

### Descriptive analysis

Statistical software for social sciences (SPSS version 27) will be used to conduct data analysis. The study of sociodemographic data will make use of descriptive statistics. Race, age, marital status, educational background, work position, and illness state, including the stage at diagnosis, chemotherapy regimen, and time since diagnosis, are all described using frequency and percentage. Before implementing the ACT intervention, inference analysis will examine the significant differences between the waiting and intervention groups. The study’s primary analysis will adhere to the intention-to-treat (ITT) principle. Furthermore, the main effect will be accompanied by a 95% confidence interval. Statistical significance will be determined using a two-tailed approach and set at p<0.05.

To address any instances of missing data, the approach will be as follows: If missing data accounts for less than 5% of the total collected data, they will be disregarded. In cases where missing data exceed 5% but fall below 40% of the total collected data and are assumed to occur randomly, multiple imputations using restricted maximum likelihood estimation will be conducted using Stata 15. However, if missing data surpass 40% of the total collected data or are presumed to be non-random or entirely random, only the available data will be utilized for analysis in the study, and any absence of data will be acknowledged as a limitation in subsequent publications of the study’s findings [41].

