### Mixed ANOVA analysis

The comparison of mean differences before and post-intervention will be examined to see whether any changes in illness cognition, anxiety, depression, psychological inflexibility, QoL, and social support among breast cancer patients in response to ACT intervention. Then, while controlling for confounders, mixed ANCOVA will be used to look at any significant changes in the measured variables between the waiting and intervention groups, with the group as the between-group factor and time as the within-group factor. A few confounding factors that may affect disease acceptance in cancer will be taken into account and controlled by using mixed ANCOVA, such as the level of pain and fatigue and monthly income [42, 43]. Age is also included as a covariance.

The effect sizes will be determined to evaluate how much patients’ perceptions of the measured variables changed with and without an ACT intervention. The formula of Cohen’s d (Rosnow Rosenthal, 1996) [44] is used to calculate the effect size. According to Cohen (1988), the effect size will be considered small if (d = 0.2), medium (d = 0.5), and large (d = 0.8).

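### The objectives assess disease acceptance at 6 and 12 months, but the Procedure and Abstract stop collecting data three months after the programme

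*Protocol article*

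**What the plan says.** The Primary objective section compares ACT with control on disease acceptance "across three-time points (T0 = baseline assessment, T1 = 4 weeks, immediately after completion of the intervention", and continues with "T2 = 6 months after commencement of the intervention, and T3 = 12 months after commencement of the intervention". It announces three time points and lists four. The Secondary objectives section repeats the same list for psychological inflexibility, for depression and anxiety, for quality of life, and for social support.

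The sections that describe data collection say something else. The Abstract (Methods) states: "Data will be collected at three points: baseline, post-intervention, and three-month follow-up". The Procedure section has the assessment batteries issued at "three specific time points: before the intervention, immediately after the intervention, and three months following the intervention".

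On programme length, the ACT intervention section says: "The ACT intervention is scheduled for 1 session per week for 4 weeks". The Mixed ANOVA analysis section specifies a mixed ANCOVA "with the group as the between-group factor and time as the within-group factor", without listing the times that make up that factor.

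**The concern.** The document gives two incompatible answers to the question of when the primary outcome is measured. The objectives rely on 6- and 12-month data that no visible text schedules. The three-month assessment that is scheduled serves no stated objective.

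Two things are at stake. First, if the Procedure is followed, the trial cannot report the longer-term comparison that its primary objective promises, and visits that were not held cannot be recovered later. Second, the within-patient factor of the main model is not fixed: its number of levels, and the follow-up it covers, depend on which section the analyst reads.

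**Working it through.** **1. Does the sample size settle which schedule is meant?** Inputs from the Participants section: "the type I error was 0.05, with a power of 0.95, three covariates, with two intervention groups and an effect size of 0.46", and 20% dropout giving 80 patients. Read 0.46 as Cohen's f (an assumption, since the text does not name the index). Use the ANCOVA F test with 2 groups, 3 covariates and 1 numerator degree of freedom.

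- Noncentrality: λ = f² × N = 0.46² × 64 = 13.54
- Denominator df: 64 − 2 − 3 = 59
- Power at N = 64: 0.951, the smallest N reaching 0.95
- With dropout: 64 / (1 − 0.20) = 80, the stated figure

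This form has no repeated-measures term, so the stated 80 does not depend on the number or timing of visits. Repeated-measures forms with the same f and an assumed within-patient correlation of 0.5 do not give 80:

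| Test | 3 time points | 4 time points |
|---|---|---|
| Between-group effect | 43 / 0.8 → 54 | 41 / 0.8 → 52 |
| Group-by-time interaction | 14 / 0.8 → 18 | 12 / 0.8 → 15 |

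The sample size therefore gives no clue to the intended schedule.

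**2. Could the two schedules be the same visits counted from different origins?** The objectives count from commencement and the Procedure counts from the end of the programme. At 4.345 weeks per month, the programme lasts 4 / 4.345 = 0.92 months. The Procedure's last assessment is then at 0.92 + 3 = 3.92 months from commencement. That is 6 − 3.92 = 2.08 months before T2 and 12 − 3.92 = 8.08 months before T3. A change of origin does not reconcile them.

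**3. The two schedules side by side, in time from commencement.**

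| Assessment | Primary objective and four secondary objectives | Abstract and Procedure |
|---|---|---|
| Baseline | yes (T0) | yes |
| End of programme, 4 weeks | yes (T1) | yes |
| About 3.9 months | no | yes |
| 6 months | yes (T2) | no |
| 12 months | yes (T3) | no |
| Number listed | 4 (called three) | 3 |

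Two of the four time points in the objectives are covered by the Procedure and two are not. One of the Procedure's three assessments is used by no objective.

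**4. Effect on the model.** With two groups, the group-by-time test has (2 − 1) × (levels − 1) numerator degrees of freedom: 2 with three time points and 3 with four. These are different tests over different follow-up periods.

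**5. Is it an isolated slip?** The 6- and 12-month list appears five times (one primary and four secondary objectives). The three-month schedule appears twice (Abstract and Procedure). Neither looks like a single mistyped line.

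**The case against.** The best case against the point has four parts.

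- **The objective is not wholly lost.** A reader might infer that the primary objective cannot be answered at all. The documents do not support that: baseline and 4 weeks are in both schedules, so the post-intervention comparison remains possible. What fails is the objective as worded, across T0 to T3. This part of the objection stands.
- **Fig 1 is not shown.** Its caption says that it holds the assessment schedule, so one cannot assert that 6- and 12-month visits are scheduled nowhere, only that no visible text schedules them. This stands as a limit. It does not remove the conflict: whichever schedule the figure carries, either the objectives or the Abstract and Procedure would still be wrong.
- **Error rate.** A reader might infer that several post-baseline visits, each tested at the level in "Statistical significance will be determined using a two-tailed approach and set at p<0.05", inflate the type I error by a calculable amount. The Mixed ANOVA analysis section plans one group-by-time model, not separate tests per visit, and repeated scores from the same patients are not independent. No such figure can be derived from the document. The decisive contrast may also be named in a statistical analysis plan that is not shown, so its absence here is not itself an error.
- **Dropout.** A reader might infer that a 12-month schedule undermines the 20% allowance. The Participants section ties that allowance to no length of follow-up, so the inference is not supported.

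**Conclusion.** The contradiction is real and needs correcting. Its size is two of four objective time points without planned data under the Procedure, one scheduled assessment that serves no objective, a last assessment at about 4 months as against 12, and a time factor with either three or four levels. In addition, the count of three is wrong within the objectives themselves.

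The conclusion rests on the visible text of the article and on reading the Procedure's three months as counted from the end of the four-week programme. It does not presume which schedule the sponsor intended. It does not alter the stated sample size, and it leaves the baseline to 4-week comparison intact.

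**What to change.** 1. Establish which schedule is actually being run. State it identically in the Abstract, the Primary and Secondary objectives, the Procedure and Fig 1, with one time origin throughout.
2. Correct the count of time points in the primary objective and in the four secondary objectives.
3. In the Mixed ANOVA analysis section, list the levels of the time factor so that they match that schedule.
4. State which time point or contrast is primary for disease acceptance. T1 is a reasonable candidate: it is the only post-baseline assessment in both schedules, and the Mediators and moderators section already uses change from before to after treatment. The choice is the sponsor's.

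**Cost.** If the three-month schedule is being run, this is a change of wording, and the objectives give up their 6- and 12-month claims. If the 6- and 12-month assessments are intended, the Procedure and Abstract must be changed to include them and the visits must be carried out, which costs more than wording. As reproduced above, the stated 80 has no term for the number of visits, so the correction alone does not change it.
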